# Abbreviations

ACT Artemisinin Combination Therapy

AE Adverse Event

AL Artemether–Lumefantrine

CHW Community health worker

DBS Dried Blood Spot

DHA Dihydroartemisinin

DHAP Dihydroartemisinin – Piperaquine

DSMB Drug Safety Monitoring Board

HC Health Centre (see RHC)

HP Health Post (see RHP)

HS RDT High Sensitivity Alere™ Malaria Ag P.f RDT

IRS Indoor-residual spraying

LOD Limit of Detection

LLIN Long Lasting Insecticide treated mosquito Net

NMCC National Malaria Control Center

RDT Rapid Diagnostic Test

PCD Passive Case Detection

PCR Polymerase Chain Reaction

RFDA Reactive Focal Drug Administration

RFTAT Reactive Test and Treat

RHC Rural Health Centre

RHP Rural Health Post

SP Sulphadoxine-Pyrimethamine

SAE Serious Adverse Event

WHO World Health Organization

# Definitions of Key Terminology

PCD Passive Case Detection – Symptomatic individuals present to a health center or health post and are tested for malaria with a rapid diagnostic test (RDT) or microscopy, and treated with an appropriate antimalarial if positive.

RFDA Reactive Focal Drug Administration – A reactive response consisting of treating all individuals within a defined radius of each RDT-confirmed incident malaria case with dihydroartemisinin-piperaquine (DHAP).

RFTAT Reactive Focal Test and Treat – A reactive response consisting of testing all individuals within a defined radius of each RDT-confirmed incident malaria case with an RDT and treating all positive individuals with artemether-lumefantrine (AL).

CHW Responses The majority of RFTAT or RFDA responses will be exclusively performed by a single CHW operating similarly to standard reactive case detection procedures in rural areas.

Research Responses These responses will augment the CHW response, with a sample collector, enumerator and supervisor. This team will also make repeat visits to follow individuals enrolled in a reactive response longitudinally.

# Health Facility hierarchy in Zambia

To avoid confusion, it is necessary to clarify terminology around health facilities. For the purposes of this document, the term rural health clinic (HC / RHC) will refer to all government run facilities that act as the primary location for health care service delivery and which are manned by professional health workers. In contrast, a rural health post (HP / RHP) is a satellite facility attached to an individual health centre that aims to expand health care access for a few key interventions, namely malaria testing and treatment. HP’s are predominantly manned by volunteer community health workers. The term health facility will refer to both HC’s and HP’s.

# Project summary

| **Primary Aim** | Compare the effectiveness of RFDA using DHAP with RFTAT using AL in achieving zero seropositivity in children under fifteen |
| --- | --- |
| **Secondary Aims** | 1. Compare the effectiveness of RFDA using DHAP with RFTAT using AL in reducing RDT confirmed malaria incidence through passive case detection at health facilities. 2. Compare the effectiveness of RFDA using DHAP with RFTAT using AL in reducing the prevalence of malaria and preventing re-infection in individuals receiving reactive responses. 3. Compare the cost-effectiveness of RFDA using DHAP with RFTAT using AL in reducing the burden of malaria in the community. 4. Measure the proportion of *P. falciparum* infections likely attributable to importation and local transmission using parasite genotyping as well as defining genotype spatial distribution. 5. Assess the utility of using serology to measure short term changes in malaria transmission and evaluate malaria elimination programs 6. Assess the feasibility of using remotely sensed malaria risk maps to identify areas with higher potential for local malaria transmission. 7. Assess the utility of a HS RDT in identifying additional standard RDT sub-patent infections in the RFDA arm |
| **Study Site & Target Populations** | Population of ~130,000 people in ~30,000 households in 16 Health Center catchment areas in Southern Province. |
| **Study design** | Cluster randomized controlled trial will be used to evaluate the impact of RFDA intervention against current standard of care for the impact on seropositivity in children under fifteen years, passive surveillance for confirmed malaria case incidence, and elimination of transmission from hotspots |
| **Primary outcome measures for assessing program impact** | 1. Malaria seropositivity in children under fifteen after two-year intervention within health center catchment areas 2. Confirmed malaria incidence as measured through routine passive case detection at health centers and health posts throughout the selected health center catchment areas |
| **Primary data collection & sampling method** | Sampling after the interventions will be used to determine malaria seropositivity in children under fifteen in each health center catchment population.  The routine government rapid reporting system will be used to determine confirmed malaria case incidence throughout the entire study area.  Longitudinal cohorts will be used to determine clearance and re-infection rates for each arm from a subset of individuals participating in reactive responses. |
| **Sample size** | - Simple random sample survey of children under fifteen in all health clinic catchments population : 8,000 - Routine reporting for malaria case incidence: ~130,000 (all ages) - Reactive responses in all areas: ~30,000 (all ages) - Re-infection / importation / serology in a subset of the study participants: ~9,000 (all ages) |
| **Statistical & analytic plan** | A difference-in-differences approach will be used to assess changes in both primary and secondary outcomes among intervention and control groups, using mixed effects logistic and Poisson models for the outcomes of parasite seropositivity and confirmed malaria incidence. Clearance and prevention of reinfection from areas receiving rapid responses will be determined through Poisson regression. Month-by-month estimates of effectiveness will be analyzed using the routine rapid reporting of confirmed malaria incidence.  We will estimate direct effects and spillover effects of the reactive, focal malaria interventions on malaria incidence and prevalence and assess whether effects vary by intervention coverage, distance to intervention, and time from incident case detection. We will then pool this data with other similar trials using fixed and random effects. |

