# Research Plan

## Study Design

The study design will be a cluster randomized trial comparing an enhanced strategy for malaria elimination (RFDA with DHAP) with the current strategy (RFTAT with AL). Impact evaluation will consist of: 1) community-based, cross-sectional measurement of malaria seropositivity in children aged ≥ 1 month and < 15 years through a random sample survey at the end (two years) of the intervention period; 2) longitudinal follow-up of a subset of individuals participating in reactive responses by a research team; and 3) detection of incident malaria cases and total outpatient attendance at health centers and health posts.

A total of sixteen health centers will be targeted in this RCT (Table 1). The proposed areas were selected from the 11 districts within Southern Province, Zambia that have successfully implemented RFTAT surveillance with the following criteria: a mean monthly incident malaria case load of < 25 and a mean test positivity during ongoing RFTAT of at least 5%. Where multiple health centers fulfilled the inclusion criteria, preference was given to those that are geographically close to one another (minimum 5km buffer to reduce contamination) and are accessible all year round. Selected health centres will be randomized to either control or intervention arms, with 8 health centers per arm (Figure 3).

| Organisation Unit | Confirmed Cases of Malaria (Sep ’13 – Aug ’14) | | | | Positivity Rate (%) during RFTAT |
| --- | --- | --- | --- | --- | --- |
|  | Clinic | Community | Total | Average cases per month |  |
| Chisekesi Rural Health Centre | 176 | 77 | 253 | 21 | 9.4 |
| Habulile Rural Health Centre | 133 | 109 | 242 | 20 | 9.3 |
| Katombora Health Post | 123 | 78 | 201 | 17 | 12 |
| Kazungula Health Post | 71 | 20 | 91 | 8 | 7.9 |
| Keemba Rural Health Centre | 58 | 89 | 147 | 12 | 6.8 |
| Mayoba Rural Health Centre | 46 | 37 | 83 | 7 | 9.4 |
| Moonde Rural Health Clinic | 0 | 214 | 214 | 18 | 8.3 |
| Mubanga Rural Health Centre | 77 | 139 | 216 | 18 | 5.3 |
| Mukwela Rural Health Centre | 86 | 157 | 243 | 20 | 7.8 |
| Munkolo Rural Health Centre | 42 | 76 | 118 | 10 | 6.9 |
| Musokotwane Health Post | 38 | 53 | 91 | 8 | 8.2 |
| Muzya Rural Health Centre | 40 | 83 | 123 | 10 | 9.9 |
| Nadezwe Rural Health Centre | 58 | 107 | 165 | 14 | 11.2 |
| Namwianga Urban Health Centre | 56 | 140 | 196 | 16 | 5.2 |
| Ngwezi Rural Health Centre | 11 | 169 | 180 | 15 | 8.3 |

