## Research Strategy by Aim

### Primary Aim

Compare the effectiveness of RFDA using DHAP with RFTAT using AL in achieving zero seropositivity in children under 15 years of age.

Hypothesis: RFDA with DHAP will be more effective in reducing malaria prevalence in the community than RFTAT using AL by clearing parasites from RDT-negative individuals with subpatent parasitemia and through the longer chemoprophylactic protection conferred by DHAP.

**Design**: Cluster randomized controlled trial in which eight health center catchment areas are randomized to RFTAT with AL (control arm) and eight health center catchment areas are randomized to RFDA with DHAP (intervention arm)

**Population**: Residents (under fifteen years of age) of a random selection of households in health center catchments within the intervention and control arms using satellite imagery to define the sampling frame

**Outcomes**: 1) malaria seropositivity measured at endline;

**Inclusion/Exclusion criteria:** All consenting individuals aged ≥ 1 month and < 15 years will be tested for parasite prevalence in the survey

**Procedures**: 1) randomization; 2) RFTAT with AL or RFDA with DHAP; 3) endline survey

**Assays**: Serological analysis of DBS collected during endline survey

**Analysis**: For the outcome of seropositivity, a comparison of seropositivity will be made between intervention and control areas and between children stratified into younger (aged ≥ 1 month to < 2 years), middle (aged ≥ 2 years to < 5 years), and older (aged ≥ 5 years and < 15 years). To account for correlated data at the cluster level, mixed effects regression models with the health center as a random intercept will be the primary analytic method to estimate the effectiveness of RFDA compared to RFTAT for the outcome of malaria prevalence as measured through seropositivity. Analyses will account for environmental factors, socio-economic status, housing construction, education level, and demographic measures of the population as well ITN coverage and indoor residual spraying.

### Secondary Aim 1

Compare the effectiveness of RFDA using DHAP with RFTAT using AL in reducing RDT confirmed malaria incidence through passive case detection at health facilities

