**Inclusion/Exclusion criteria:** All consenting individuals aged ≥ 1 month will be tested for parasite prevalence 0, 30 and 90 days following the reactive research response. Individuals to be included in the assessment of secondary aim 2 will have parasite measurements at 0, 30 and 90 days following the reactive research response.

**Procedures**: 1) reactive response; 2) follow-up visit at 30 days; 3) follow-up visit at 90 days

**Assays**: PCR for asexual parasites using DBS collected at 0, 30 and 90 days

**Analysis**: Parasite prevalence at 30 days and 90 days will be analyzed separately. Areas receiving a reaction will form the unit of analysis while malaria infections during returns to the areas receiving a reaction will be measured as a count variable. A mixed effects Poisson regression with the offset being the number of individuals providing filter paper with a DBS during the return to the areas receiving a reaction will be used to compare the effectiveness of RFDA v. RFTAT at clearing an area of malaria infections (30 days) and preventing reintroduction following the reactive response (90 days). A number of factors will be tested for acting as effect modifiers through a test for interaction including initial parasite prevalence at day 0 during the response, response coverage in the area, asset-based wealth index, vector control coverage of the area, age and demographics of the individuals living in the area, as well as environmental factors such as vegetation cover and topographical measures. A fixed effects regression approach, wherein the difference between the number of malaria-infected individuals at day 0 during the reaction and the number of malaria-infected individuals at day 30 and/or day 90 following the reaction may be used to assess how the malaria parasite reservoir changes following the reactive responses.

### Secondary Aim 3

Compare the cost-effectiveness of RFDA using DHAP with RFTAT using AL in reducing the prevalence of malaria in the community.

Hypothesis: RFDA will be more cost-effective in reducing malaria prevalence than RFTAT by clearing parasites from individuals with subpatent parasitemia, through the longer protective effect conferred by DHAP, and the cost savings of not using a diagnostic test (RDT).

**Design**: cluster randomized trial

**Population**: all residents of the health center catchment areas within the intervention and control arms

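### Secondary Aim 2: the summary plans Poisson regression with no cluster term, section 2.8.3 a mixed effects Poisson model, and neither ties the arm comparison to the randomised health centre

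*Protocol*

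**What the plan says.** The Project summary (Statistical & analytic plan) first describes the other outcomes, "using mixed effects logistic and Poisson models for the outcomes of parasite seropositivity and confirmed malaria incidence". Its next sentence turns to Aim 2: "Clearance and prevention of reinfection from areas receiving rapid responses will be determined through Poisson regression". No random effect or cluster adjustment is mentioned there.

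Section 2.8.3 (Secondary Aim 2, Analysis) sets the unit: "Areas receiving a reaction will form the unit of analysis". It then gives the model: "A mixed effects Poisson regression with the offset being the number of individuals providing filter paper with a DBS". Days 30 and 90 are analysed separately. The grouping level of the random effect is not named.

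The Primary Aim (section 2.8.1) does name it: "mixed effects regression models with the health center as a random intercept will be the primary analytic method". The Study Design section randomises health centres, eight to each arm. Section 2.4.1 draws index cases for research responses in equal numbers from each clinic, so every centre contributes several response areas.

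**The concern.** The protocol describes one comparison with two model labels. The summary's label follows directly on a sentence that says mixed effects for other outcomes, so its absence for Aim 2 can be read as deliberate. Section 2.8.3 would settle this if it placed the random effect on the health centre, but it makes the response area the unit and leaves the level open.

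Response areas in one centre share that centre's transmission level and its arm. An analysis without a centre term treats them as independent evidence about the arm. Chance differences between two sets of eight centres could then be reported as an effect of RFDA on clearance (day 30) or on preventing reintroduction (day 90). Aim 2 is the protocol's direct test of both.

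**Working it through.** **The plan's own figure.** The protocol gives no power, prevalence, between-centre variation or error rate for Aim 2. Its only sample-size calculation is for the endline survey (section 2.9), which is also the only source of a between-centre coefficient of variation k. I reproduced that first, to confirm what k means:

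c = 1 + (1.960 + 0.842)² × {[p0(1−p0) + p1(1−p1)]/m + k²(p0² + p1²)} / (p0 − p1)²

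With p0 = 0.05, a 61.7% reduction (p1 = 0.01915), m = 500 and k = 0.5, c = 8.0 centres per arm. This matches the bold cell of Table 3, so k is the between-centre coefficient of variation of the true rate. (The text above that table gives 64.5% instead. That is a separate matter and does not enter here.)

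**Inputs for Aim 2**
- Centres: 8 per arm (Study Design).
- Fewest responses: two per month per arm (section 2.4.1) over 24 months is 48 per arm, and 48/8 = 6 per centre.
- Most responses: about 9,000 people in the cohort (Project summary, Sample size), and 9,000/16 = 562 per centre. At an assumed 25 people per response this is about 22 responses.
- k: 0.3 to 0.5, borrowed from Table 3.
- PCR prevalence at follow-up: 1% to 5%, assumed.

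**Plain Poisson with no true effect.** With m people per centre and prevalence p, the variance of a centre's count exceeds the Poisson variance by the factor V = 1 + m·p·k². A test that ignores this rejects with probability 2[1 − Φ(1.96/√V)].

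| Responses per centre | m | p | k | V | False positives |
|---|---|---|---|---|---|
| 6 | 150 | 1% | 0.3 | 1.135 | 6.6% |
| 6 | 150 | 1% | 0.5 | 1.375 | 9.5% |
| 6 | 150 | 5% | 0.3 | 1.675 | 13.0% |
| 6 | 150 | 5% | 0.5 | 2.875 | 24.8% |
| 22 | 550 | 1% | 0.3 | 1.495 | 10.9% |
| 22 | 550 | 1% | 0.5 | 2.375 | 20.3% |
| 22 | 550 | 5% | 0.3 | 3.475 | 29.3% |
| 22 | 550 | 5% | 0.5 | 7.875 | 48.5% |

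Simulation over the same ranges gave about 6% to 48%. Adding variation between response areas (assumed coefficient of variation 0.5) moves the top setting to around 50%.

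**If the 9,000 are samples.** Should that figure count samples over three visits, there are about 188 people per centre, and the range for the same k and p is about 7% to 28%.

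**Models that respect the centre.** In simulation, a health-centre random intercept judged against the normal distribution gave about 4% to 10%, with 9% to 11% in the most extreme setting. A t-test on the 16 centre values gave about 4% to 5%.

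**The case against.** The strongest reply is that section 2.8.3 is the operative text and already asks for a mixed effects model. A mixed effects Poisson model is a kind of Poisson regression, so the summary may simply be shorthand. The exact random-effect structure, overdispersion and small-sample degrees of freedom are usually left to a statistical analysis plan, which is not shown. Most of this stands: the unnamed level would not be a finding by itself. What remains is that the protocol labels one comparison in two ways and ties neither to the randomised unit, although it does so for the Primary Aim.

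The baseline offers a second defence. The summary announces a difference-in-differences approach for primary and secondary outcomes, and day 0 is measured. Stable centre differences would largely cancel in such a contrast. Section 2.8.3 makes the change-from-day-0 analysis optional, however, and the cancellation weakens if centre effects shift over time. This is mitigation, not a cure.

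Three stronger readings are tempting, and the documents do not support them:
- A reader might infer that Aim 2 will in fact run at a false-positive rate of up to one in two. That requires following the summary literally and taking the least favourable inputs, none of which the protocol states for Aim 2.
- A reader might infer that the random effect in section 2.8.3 must sit either on the area or on the centre, so that one source of variation is always missed. Nothing there limits the model to one random effect; areas nested in centres is an ordinary mixed model.
- A reader might infer that the planned effect-modifier tests are themselves badly inflated. That needs a centre-only random effect and an area-level variation for which the protocol gives no figure.

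**Conclusion.** The point holds as an inconsistency with a real but conditional consequence. The summary and section 2.8.3 describe different models for Aim 2, and neither names the health centre. A Poisson analysis with no centre term would exceed 5% false positives at every setting in the table, from about 6% to about 50%. The position in that range depends on a k borrowed from the endline calculation, an assumed PCR prevalence, an assumed 25 people per response, and the reading of about 9,000 as people.

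The protocol does not clearly intend that analysis. A mixed model with a health-centre intercept removes most of the excess, and inference on between-centre degrees of freedom addresses the rest. As this concerns a secondary aim and is easily repaired, it should be corrected but does not undermine the trial.

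**What to change.** Reword the Aim 2 sentence in the Project summary so that it names the same mixed effects model as section 2.8.3. In section 2.8.3, state:
- a random intercept for health centre;
- an allowance for extra-Poisson variation between response areas, through a negative binomial model or an area-level random effect (Secondary Aim 1 already permits a negative binomial model);
- the offset as now written;
- the arm effect judged on 16 − 2 = 14 degrees of freedom, or checked by a t-test on the 16 centre rates.

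The cost is a few lines of text and no new data. Intervals become somewhat wider. Moving from the normal to the t distribution with 14 degrees of freedom widens them by 2.145/1.960 = 1.09, about 9%. Against a plain Poisson analysis the standard error grows by roughly √V, which is the uncertainty that randomising 16 centres actually carries.

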# Background

## Introduction

The Zambia National Malaria Strategic Plan (2011-2016) calls for the creation of five malaria-free zones by 2015

^1^. Enhanced malaria surveillance has been expanded to cover a large portion of Southern Province, an area with a documented decline in malaria prevalence to <10% during Malaria Indicator Surveys (MIS) conducted in 2006, 2008, 2010, 2012 and 2015

^2–6^. The enhanced surveillance data suggest some areas within Southern Province are candidates for eliminating malaria and documenting zero transmission; however, questions remain about the strategies required to move from very low to zero transmission as well as how to document zero transmission.

Implementing and maintaining a high quality surveillance and passive case detection (PCD) system throughout the target population is critical to achieving elimination

^7^. Even with universal access to malaria diagnosis and treatment, however, passive case detection PCD will not identify asymptomatic infected individuals

^8^. Reactive case detection is a method to identify and clear these hidden reservoirs, which are often spatially clustered in a population

^9^. In areas of low transmission, incident malaria cases can be used as an indicator of local malaria transmission

^10^. A reactive response uses incident cases as the means to target a specific geographical area where the probability of additional infected individuals is higher than in the general population

^9^.

In Southern Province, a reactive focal test and treat (RFTAT) strategy to reduce foci of infection has been implemented by the National Malaria Control Program since 2012 (Appendix 1), which was adapted from an urban reactive case detection programme (Appendix 2). In rural areas this strategy consists of testing all individuals within approximately 140 meters of an incident malaria case confirmed by rapid diagnostic test (RDT) and treating all positive individuals with artemether-lumefantrine (AL) (or referring as appropriate). In the context of malaria elimination in Zambia, this strategy has been termed Step D as it comprises the community-level surveillance system that accompanies a series of other steps (Figure 1), including Step B (health center based malaria rapid reporting system) and Step C (mass screen and / or treat activities in moderate transmission zones), all of which are active in Southern Province. A number of questions remain about the Step D approach, including its sensitivity to identify residual foci of malaria transmission, the appropriate spatial scale of the reaction, the implications of using an imperfect diagnostic test to direct treatment, and the overall effectiveness of the strategy to reduce malaria transmission to zero.

[figure not shown]

Figure 1 – Schematic highlighting the overall Malaria Control and Elimination Partnership for Africa (MACEPA) concept for malaria interventions across a range of transmission intensities.

